## Abstract

**Background:**

Physical activity levels are low in people with Parkinson’s disease (PD) and have proved difficult to increase with exercise programs alone. Intervention approaches that address both the capacity to engage in physical activity and self-management strategies to change and maintain exercise behaviours are needed to address this intractable issue.

**Methods:**

This will be an assessor-blinded, randomized controlled trial performed in Brisbane, Australia. Ninety-two people with mild-moderate PD will be randomly allocated to two groups: usual care, and a physiotherapy-led group exercise program combined with self-management strategies. In the intervention group, twelve, 80-min sessions will be conducted over 4 weeks in groups of up to 4 participants. The intervention will consist of circuit training including treadmill walking to target aerobic fitness, and activities targeting strength, balance, and gait performance. In addition, each session will also incorporate strategies focusing on self-management and behaviour change, augmented by the provision of a fitness activity tracker. Outcome measures will be collected at baseline (T1), immediately post intervention (T2) and at 6 months follow-up (T3). The primary outcome measure is free-living physical activity (average daily step count over 7 days) at pre (T1) and post (T2) intervention measured using an activPAL™ device. Secondary outcome measures captured at all time points include time spent walking, sedentary and in moderate intensity exercise over 7 days; spatiotemporal gait performance (step length, gait speed, endurance); health-related quality of life; and outcome expectations and self-efficacy for exercise.

**Discussion:**

Sustainability of gains in physical activity following exercise interventions is a challenge for most populations. Our incorporation of a chronic disease self-management approach into the exercise program including fitness tracking extends previous trials and has potential to significantly improve free-living physical activity in people with PD.

**Trial registration:**

This study has been prospectively registered in Australian and New Zealand Clinical Trial Registry (ACTRN12617001057370), registered on 19/07/2017. Available from www.anzctr.org.au/ACTRN12617001057370.aspx.

## Introduction

### Background and rationale {6a}

Despite pharmacological intervention, people with Parkinson’s disease (PD) show a steady decline in physical functioning due to cumulative deficits in motor and non-motor impairments. Physical activity is important to maintain in people with PD, as it not only contributes to maintaining functions such as gait, balance in standing, and muscle strength, but these contribute to safe performance of activities of daily living and maintenance of independence. One area of decline is in physical activity. Levels of physical activity are lower in people with PD than healthy controls [1–3] and have been shown to decline overtime without intervention [4].

While a Cochrane review has found that exercise-based interventions can lead to short-term improvements in gait and function in people with PD [5], longer-term changes are difficult to achieve [6]. Physical activity behaviour is complex and multifactorial. Identified barriers to physical activity in people with PD include exercise self-efficacy and fear of falling [7]. Qualitative findings indicate that feedback and motivation influence decision making with regards to exercise participation in people with PD [8]. The largest study of intervention to improve physical activity in PD used personalized motivational coaching alone which was no more effective at increasing self-reported physical activity in sedentary people with PD than advice promoting safe movement [9]. Post hoc analysis however revealed that those participants with greater levels of physical fitness and better walking ability demonstrated greater increases in physical activity than the control group [10]. Intervention to improve levels of physical fitness and walking ability may therefore be an important component of promoting physical activity behaviour change in this population.

Randomized controlled trials have demonstrated that regular aerobic exercise is achievable for people with PD and can contribute to improved fitness [11, 12] and slowing the progression of symptoms over 3 to 6 months [13, 14]. Prescribed exercise programs including stationary cycling, stationary trainers and treadmill walking have all shown positive results when performed for at least 30 min, 3 times each week at moderate and high intensities, with high-intensity training proving more beneficial for slowing progression of primary impairments [13]. The ongoing engagement in physical activity following a prescribed exercise program is a challenge however, and education about and performance of exercise alone may not be sufficient to change behaviour. Personal factors such as self-efficacy for exercise, motivation, or fear of falling, and environmental factors such as social support, accessibility or poor weather are often barriers identified to start or remain engaged in exercise in people with PD and should be addressed [7, 15].

Several self-management approaches for people with chronic disease can together address these factors. The Health Action Process Approach [16] consists of two phases—a motivational phase where beliefs drive activities, and a volitional phase where self-regulatory skills and strategies (action planning, coping planning, recovery self-efficacy and social support) are employed to translate intentions into action [17]. Goal Setting Theory [18] underpins goal development which drives the volitional phase of action. Finally, self-determination theory can also be applied to intervention design to enhance understanding, motivation and thus engagement with an intervention [19], addressing the need for competence, autonomy and relatedness. Few studies have evaluated the impact of self-management approaches to improve physical activity or exercise update in people with PD [20–22]. These have varied in design, population studied, aim and type of intervention, and outcomes measured, with heterogenous results found to date.

### Objectives {7}

This trial aims to determine if a small group physiotherapist-led exercise program combined with a self-management approach is more effective than usual care at promoting increased physical activity in people with mild to moderate Parkinson’s disease. Data will be collected at baseline (T1), immediately following intervention (T2, +4 weeks) and 6 months after intervention (T3, +26 weeks).

Small group physiotherapist-led exercise sessions will be used to address participants’ physical fitness, confidence and motivation to get going and keep going with exercise. Physical fitness will be addressed by ensuring that a primary component of the group exercise will be using treadmill training to ensure participants work at a moderate-high heart rate (60–80% HRR) for 30 min every session. This trial extends previous work by using this training to explicitly improve exercise self-efficacy (or belief they can exercise) and by adding it to a self-management framework to help people with PD keep exercising.

This project aims to determine if a group program of exercise aimed to increase physical fitness and gait performance incorporated with a self-management approach results in a greater and more sustained improvement in free-living physical activity (steps/day) and secondary outcomes than usual care.

### Trial design {8}

This study is a two-arm, parallel group, assessor-blinded randomized controlled superiority trial. Randomization will be performed in variable block permutations by an offsite person independent to the study with a 1:1 allocation ratio.

## Methods: participants, interventions and outcomes

### Study setting {9}

The study is planned to be conducted in multiple sites within the metropolitan south-east region of Queensland, Australia, including a university gait laboratory, and in the gym of hospital or community-based physiotherapy outpatient services. This region has a population size of approximately 3.8 million and includes the capital city, Brisbane.

### Eligibility criteria {10}

The inclusion criteria for participants are as follows: a diagnosis of idiopathic PD confirmed by a neurologist; Modified Hoehn & Yahr stage I to III; living in the community; able to attend assessment and intervention sessions; a Montreal Cognitive Assessment Scale (MoCA) score of >23/30 [23]; and willing and able to provide consent. Exclusion criteria include people who have had surgical management of their PD (e.g. deep brain stimulation); a diagnosis of any other neurological disorders, uncorrected sensory deficits, or medical conditions that may limit their ability to safely exercise; and people who report that they are already meeting physical activity guidelines for older adults (exercising for >150 min/week at a moderate intensity).

### Recruitment {15}

Calls for participants will be made via local neurologists, physiotherapists, Parkinson’s support organizations and social media. All study procedures will be discussed individually with volunteers by a member of the research team, who will clarify any questions, before screening for eligibility.

### Who will take informed consent? {26a}

Following this, informed written consent will be signed voluntarily by participants and witnessed by the researcher responsible for gaining informed consent.

### Additional consent provision for collection and use of participant data and biological specimens {26b}

No biological specimens will be collected as part of this trial. At the completion of the trial, participants will be provided with an opportunity to provide consent to be contacted by trial investigators for any future studies.

## Interventions

### Explanation for the choice of comparators {6b}

Usual care for people with mild-moderate PD in Australia includes advice and education about exercise and opportunities to exercise which can come from multiple disciplines including medical professionals (e.g. neurologists), physiotherapists and exercise professionals. Including a comparator of usual care allows us to evaluate the real-world impact of implementing the trial intervention in the current health care setting.

### Intervention description {11a}

Participants in the intervention group will take part in twelve, small group (max 4 participants) structured exercise sessions over 4 weeks, each 75–80 min in duration, led by a registered physiotherapist trained to provide the intervention. Exercise sessions will include a short group warm up followed by a structured circuit of 30 min of aerobic exercise training, lower limb progressive resistance strength training, balance and gait retraining, followed by a cool down session. Aerobic exercise training will occur primarily via walking on a treadmill at an intensity of 60–80% of heart rate reserve determined using the Karvonen formula (i.e. Target Heart Rate = ((max HR − resting HR) × 60–80%) + resting HR). As exercise tolerance improves, walking speed and incline of the treadmill will be increased to maintain this level of intensity over the 12 sessions [12].

Progressive resistance strength training will target the hip and knee flexors and extensors, hip abductors and ankle plantarflexors. Three sets of eight repetitions of each exercise will be performed at 40–60% of the participants one repeat maximum (1RM), with resistance increased by 5% when participants are able to achieve 10 repetitions at 60% of their 1RM [24]. Resistance exercises will be performed using both variable resistance equipment and functional resistance exercises [25] depending on what is available to the participant after the 4 weeks of supervised exercise to maximize carryover to the home environment. Individualized balance and gait retraining exercises will be prescribed as indicated for each participant incorporating the principles of movement strategy training [26] and highly challenging balance retraining [27].

The self-management approach will be delivered during the same 4-week period that participants are participating in the exercise groups. It will involve 5–10-min sessions, delivered individually to the participants by the physiotherapists prior to or during the exercise sessions. Behaviour change techniques used in this self-management approach will include education, behavioural instruction, self-monitoring, goal setting and goal review, feedback, problem solving, action planning and coping planning to encourage initiation and maintenance of physical activity. At the first exercise session, participants in the intervention group will receive information and a workbook to encourage self-monitoring of physical activity and guide participants through the process of setting short- and long-term goals as well as formulating action plans and coping strategies. During the 4 weeks of exercise sessions and the following 6 months, participants will also be provided with a Garmin Vivosmart fitness tracker that monitors and sets goals for physical activity (number of steps / day), and records heart rate, and distance travelled. Participants will be instructed in how to use the device and associated application/software, and their self-monitoring ability will be tracked during the 4 weeks with the physiotherapist. During the follow-up period participant activity will be monitored monthly via the online Garmin platform. If a reduction in activity level is noted the participant will be contacted by phone to check in and to discuss their physical activity goals and achievements.

### Criteria for discontinuing or modifying allocated interventions {11b}

All participants will receive their allocated intervention unless the participant chooses to discontinue. In the event of illness or injury related or unrelated to the trial, the specific exercise intervention may need to be modified. All data will be analyzed on an intention to treat basis, where participants will be analyzed according to their original group assignment.

### Strategies to improve adherence to interventions {11c}

Strategies to improve adherence to the intervention are inherent in the self-management component of the intervention. There are no additional strategies.

### Relevant concomitant care permitted or prohibited during the trial {11d}

All participants will continue with their usual pharmaceutical care during the trial. There is no restriction on accessing external therapy or exercise groups.

### Provisions for post-trial care {30}

In the event of an adverse event or harm because of their participation in the trial will be provided with relevant ongoing care under the trial insurance.

### Outcomes {12}

The primary outcome measure is free-living physical activity (average number of steps per day) at post intervention (T2) assessment collected via an activity monitor (activPAL™) that will be worn for seven complete 24-h periods.

Secondary outcomes will include (a) free-living physical activity (average number of steps per day) at follow-up (T3); (b) additional measures of free-living physical activity (average daily time spent walking, average daily time spent sedentary) at each assessment time point; (c) gait endurance measured via the 6-min walk test at each assessment time point; (d) spatiotemporal gait parameters (step length, gait speed) during single and dual task conditions over 8 m using a GAITrite™ electronic walkway at each assessment time point; and (e) health-related quality of life (QOL) at each assessment time point; will be measured using the 39-item Parkinson’s disease questionnaire (PDQ-39).

### Participant timeline {13}

The participant flow is shown in Figs. 1 and 2. All participants will be engaged in the study for 6 months. Assessments will be conducted at baseline (T1 = week 0), post intervention (T2 = +week 5) and at 6 months follow-up (T3 = week 26). Allocation to intervention will occur on completion of the baseline assessment.

**Fig. 1 Fig1:**
[figure not shown]
Schedule of enrolment, interventions, and assessments

**Fig. 2 Fig2:**
[figure not shown]
Participant flow

### Sample size {14}

The required sample size has been determined to be 92 participants (46/group) to detect a 22% increase in the number of steps/day immediately following the 4-week intervention. The proportion of change is based on previous studies of people with mild-moderate idiopathic PD who volunteered for exercise trials [1]. This determined a need for 41 participants per group. A conservative 12% allowance for withdrawals was included based on previous exercise trials in people with Parkinson’s disease [9]. Sample size was calculated using SPSS.

## Assignment of interventions: allocation

### Sequence generation {16a}

Computerized random numbers were generated in variable block permutations of 4 or 6 using Matlab™.

### Concealment mechanism {16b}

To conceal randomization, an independent offsite researcher will create the schedule and prepare consecutively numbered opaque envelopes with the group allocation of each participant sealed inside and locked in a location inaccessible to the assessors.

### Implementation {16c}

After completing all baseline assessment requirements, participants will be contacted by phone to receive their group allocation. Participants allocated to the intervention group are scheduled to attend the group exercise sessions. The allocation phone call is made to participants by a member of the research team involved in intervention, but not responsible for any assessment.

## Assignment of interventions: blinding

### Who will be blinded {17a}

The study is a single-blind design where assessors are blinded to participant allocation. The randomization schedule has been prepared and concealed by a researcher separate to this research study. Allocation is revealed following baseline assessment and is revealed to participants by a researcher who is independent to the assessment of outcomes (one of the intervention physiotherapist/researchers). The randomization envelopes will be used to reveal each participant allocation in turn, to ensure that the researchers who provide the intervention remain blinded to all future allocations. Participants are reminded at the time of allocation and before their post and follow-up assessments that the assessor cannot be told who has been allocated to which group. Participants in the intervention group are additionally asked not to wear the activity monitoring watch on the day of their assessments. Data analysis will be completed by an individual blinded to group allocation.

### Procedure for unblinding if needed {17b}

There is no forseeable reason for the assessor to be unblinded to participant allocation. Members of the research team independent of the assessment of outcomes will be responsible for managing any event that may require knowledge of the participant allocation.

## Data collection and management

### Plans for assessment and collection of outcomes {18a}

All assessments will be conducted by a registered physiotherapist who has had specific training in the conduct of all outcome measures.

## Physical activity

Participants will wear an activity monitor (activPAL™) fixed to the anterior thigh using a waterproof adhesive dressing continuously for nine consecutive days at each assessment point. The activPAL™ is a lightweight electronic logger that contains a microprocessor, sensing element (accelerometer, gyroscope), recording element, associated electronics and power supply. It has demonstrated excellent accuracy measuring step count during treadmill and outdoor walking, with some terrain challenges and attention demands, at a variety walking speeds in people with PD [28]. The activPAL™ has been used to quantify sedentary behaviour [29] and ambulatory activity [3, 30] in people with PD.

Step count data from the seven complete 24-h (midnight to midnight) periods will be averaged to give steps/day. Additional measures of free-living physical activity (e.g. average daily time spent walking, average daily time spent sedentary, total minutes/week spent in moderate intensity exercise, time spent in bouts of activity) will be drawn from the 7 days of activPAL™ recording at each of the three assessment time points. The proportion of people meeting American College of Sports Medicine physical activity guidelines with respect to volume of physical activity will also be calculated (Garmin vivoSMART).

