## Statistical methods

### Statistical methods for primary and secondary outcomes {20A}

To determine if there are differences between groups in physical activity outcomes post intervention, linear mixed models will be performed investigating group (intervention vs. control), time (baseline, post, follow-up) and group × time interactions for all variables. Baseline participant characteristics will be compared between groups and those with any differences included as covariates. Post hoc univariate testing will be undertaken if main effects and interactions are significant.

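### Guideline attainment is to be taken from the Garmin tracker, which is described only as part of the intervention, so this supplementary measure cannot be compared between arms or with baseline.

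*Protocol article*

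**What the plan says.** All places are in the protocol article.

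- **Physical activity section (data collection).** Participants wear the activPAL "continuously for nine consecutive days at each assessment point". Seven full days of it give steps per day. Walking time, sedentary time, weekly minutes at moderate intensity and activity bouts are drawn from the same recording at the three time points. The closing sentence then names another device for the proportion meeting American College of Sports Medicine "guidelines with respect to volume of physical activity will also be calculated (Garmin vivoSMART").
- **Intervention description {11a}.** "During the 4 weeks of exercise sessions and the following 6 months, participants will also be provided with a Garmin Vivosmart fitness tracker". The sentence follows the one on the workbook given to the intervention group. The tracker sets step goals, and its data are reviewed monthly during follow-up.
- **Abstract, Methods.** The self-management content of the intervention sessions is "augmented by the provision of a fitness activity tracker". The Discussion also counts the tracker among the components of the intervention.
- **Who will be blinded {17a}.** "Participants in the intervention group are additionally asked not to wear the activity monitoring watch on the day of their assessments".
- **Explanation for the choice of comparators {6b}.** Usual care "includes advice and education about exercise and opportunities to exercise". No tracker is mentioned.
- **Participant timeline {13}.** "Allocation to intervention will occur on completion of the baseline assessment".
- **Statistical methods {20A}.** Linear mixed models are planned for group, time (including baseline) and "group × time interactions for all variables".
- **Outcomes {12}.** Guideline attainment is in neither the primary nor the secondary list.

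**The concern.** The trial asks whether the program raises physical activity more than usual care does. A measure of activity helps to answer that only if both arms supply it, preferably from the same instrument and with a baseline value. Guideline attainment is tied to a device that the article places in one arm and only after randomization.

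Followed as written, the trial would report an uncontrolled proportion from the intervention arm. That figure is easy to misread. People who report already meeting activity guidelines are excluded at entry, so almost any later proportion could look like a gain. Part of it could come from the change from self-report to a device, and there would be no control figure to set against it.

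The tracker is also the feedback and goal-setting tool. Its record depends on continued wear, and those who stop using it may be the least active.

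**Working it through.** The article gives no figure to reproduce. The check follows the device, its recipients and the timing through the text.

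**Step 1: source.** Within one section, steps, walking time, sedentary time, moderate-intensity minutes and bouts come from the activPAL. Only guideline attainment is assigned to the Garmin.

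**Step 2: who has each device.** The activPAL instruction applies to participants without distinction of arm. The Garmin appears in the intervention description and is listed as an intervention component in the abstract and the Discussion. The blinding section asks only the intervention group to leave the watch off on assessment days; that request would be needed in both arms if both had watches. The description of usual care has no tracker.

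**Step 3: when.** Allocation follows completion of baseline, and the Garmin is supplied from the exercise sessions onward. No Garmin record is therefore described at T1 in either arm.

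**Step 4: which cells can be filled.** Two arms × three time points = 6 cells.

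| | T1 | T2 | T3 |
|---|---|---|---|
| Intervention, Garmin | none described | available | available |
| Usual care, Garmin | none described | none described | none described |
| Both arms, activPAL | planned | planned | planned |

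The Garmin can fill 2 of 6 cells and the activPAL 6 of 6. With the planned 46 per group, Garmin data are described for none of the 46 controls at any time and for none of the 92 participants at T1.

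**Step 5: what can be estimated.** Let p(arm, time) be the proportion meeting the guideline.

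- Between-arm difference at T2: p(intervention, T2) − p(control, T2). The second term has no data.
- Change from baseline in the intervention arm: p(intervention, T2) − p(intervention, T1). The second term has no data.
- Difference in change between arms: needs four cells, of which one is available.

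The same holds at T3. Only the two single-arm proportions, and the change between them from T2 to T3, remain.

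**The case against.** **It is not a declared outcome.** This stands. The measure is missing from the outcome list and from the abstract, and appears in one closing sentence. No hypothesis or sample size depends on it. It limits the severity but does not remove the inconsistency.

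**No contrast is stated for it.** The sentence says only that a proportion will be calculated, and the mention of three time points belongs to the preceding activPAL sentence. A one-arm descriptive figure is a possible reading and would fit the monthly Garmin review. But the sentence sits under outcome collection, follows measures taken in both arms, and refers to people in general. If a one-arm description is meant, the article should say so.

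**Controls might also have a Garmin.** No sentence rules this out, so a reader who states as fact that no control has one goes beyond the text. The placement of the device and the blinding instruction make it a strong inference. If controls did wear one, they would receive a goal-setting device that is part of the tested intervention, so that reading would also need correcting.

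**Wrong model.** A reader might infer from "group × time interactions for all variables" that a linear model is prescribed for a yes/no outcome. The documents do not firmly support this. It is a general sentence in a condensed article, and the measure is not in the outcome list. The model for an unlisted binary measure can be left to an analysis plan.

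**The activPAL may be the weaker source for intensity.** The article supports its accuracy for step count, not for classifying moderate intensity, whereas the Garmin records heart rate. This stands as a small cost of the fix. It does not supply the missing control and baseline data.

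**Conclusion.** The point holds for a supplementary measure. As described, guideline attainment comes from a device that only the intervention arm is said to receive, and only after baseline. It can be observed in 2 of 6 arm-by-time cells and allows neither a between-arm comparison nor a change from baseline.

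The conclusion assumes that controls are not given a Garmin for assessment and that no one wears one at T1. Both are inferred from where the device appears in the text.

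The severity is minor to moderate. A reader might take this as a flaw in the trial's main comparison. It is not: steps per day at T2 and the listed secondary outcomes come from the activPAL, clinic tests or a questionnaire and do not use the Garmin. A reader might also take the entry criterion of more than 150 min/week as the threshold for this measure. That figure belongs to a self-report exclusion under guidelines for older adults, a differently named source, and the Physical activity section gives no threshold of its own.

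**What to change.** 1. Replace the Garmin as the source. Derive guideline attainment in both arms at T1, T2 and T3 from the weekly moderate-intensity minutes that the activPAL recording is already planned to give.
2. State the guideline threshold that is applied, and how moderate intensity is defined from activPAL data, since the accuracy evidence cited concerns step count.
3. Compare arms at T2 and T3 with a method for binary data, for example a logistic mixed model or generalized estimating equations.
4. Report Garmin data only as descriptive information on adherence or activity in the intervention arm, and label them so. If controls are in fact given a Garmin, say so and explain how the comparison with usual care is protected.

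The cost is a few sentences. The activPAL data are collected anyway, so no participant needs a further measurement and the change can be made while the trial is running. The remaining drawback is the less well documented intensity classification, which would apply to both arms alike in its definition.
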